#### Sample size calculation

The sample size was calculated based on two-sided non-inferiority test with for 80% power and a significant level of 0.05, one-sided. We assume that the rate of postoperative complications on day 30 will be 15% in the TME group and 15% in the LE group, with a non-inferiority margin of 15%. Based on these calculations, a total of 67 patients should be allocated to each group; assuming a 5% dropout rate, we plan to enroll 140 patients. The 15% rate of postoperative complications cited above is based on published findings [26–28, 30].

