### Data analysis

The intent-to-treat (ITT) analysis set will include all subjects who are randomized into a surgery group. The modified ITT analysis set will include all subjects who undergo pre-CRT. The per protocol (PP) analysis set will include only the subjects in the ITT group who complete the study protocol. Patients who withdraw informed consent or who develop serious adverse events will be excluded from the PP analysis set. The modified ITT set will be used for analysis of primary and secondary study endpoints. The PP analysis set will be used for subgroup analysis. Baseline characteristics will also be analyzed in the ITT group.

Variables and outcomes will be analyzed using chi-square tests (for proportions) or Fischer’s exact test, as appropriate. Continuous data will be analyzed using Student’s t-test or Mann-Whitney U tests, as appropriate. Cumulative risk rates will be calculated using the Kaplan-Meier method and compared using log-rank tests. Multivariate analyses using binary logistic regression will be used to assess the risk of postoperative complications. Statistical significance will be defined as *p* < 0.05, and all analyses will be performed using SPSS software, version 22 (IBM Corporation, Armonk, NY, USA).

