In terms of postoperative complications, only one patient (2.1%) in our previous study developed a postoperative complication (perianal fistula) that required prolonged hospitalization [27]. In a recent prospective study of LE in patients with T2 rectal cancer, surgery-related adverse events above grade 3 occurred in 16 patients (21%) and grade 1 or 2 complications occurred in 50 patients (65%) [26]. Although complications of LE after pre-CRT are generally less severe than complications of TME, the rate of overall complications including dehiscence of the rectal suture line resulted from anal pain are higher than TME after pre-CRT [26]. Based on the assumption that the oncologic outcomes of LE and TME are similar for patients with a favorable response (mrTRG 1 or 2) after pre-CRT, further prospective studies on surgical outcomes in LE after pre-CRT are needed.

Pre-CRT followed by LE causes minimal loss of anorectal function and quality of life, similar to watchful waiting [26]. TME results in postoperative loss of anorectal, urinary and sexual function, and also carries the risk of permanent stoma formation [10]. In mid-to-low advanced rectal cancer, the use of pre-CRT has decreased the rate of permanent stoma formation; however, in our recent study, approximately 30% of patients receiving TME after pre-CRT did develop a permanent stoma [27]. A recent prospective study suggested that pre-CRT followed by LE might be an alternative to TME for patients with rectal cancer who have a favorable response to pre-CRT or who seek organ preservation because the Fecal Incontinence Severity Index (FISI) score and the Functional Assessment of Cancer Therapy-Colorectal (FACT-C) scores did not substantially decrease after surgery [26].

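### The sample-size statement gives the non-inferiority test two different sides, and 67 patients per arm does not follow from its stated inputs (71 at one-sided 0.05, 89 at one-sided 0.025)

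*Protocol article*

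**What the plan says.** The Sample size calculation section of the Protocol article defines the test and its level in one sentence: "The sample size was calculated based on two-sided non-inferiority test with for 80% power and a significant level of 0.05, one-sided". It assumes complication rates at day 30 of "15% in the TME group and 15% in the LE group" and a non-inferiority margin of 15%. It concludes that "a total of 67 patients should be allocated to each group; assuming a 5% dropout rate, we plan to enroll 140 patients". The 15% is attributed to four cited references.

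The Data analysis section sets a general criterion: "Statistical significance will be defined as" p < 0.05, with no side. The tests it names for proportions are the chi-square and Fisher's exact tests.

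The Primary outcome section counts events of Clavien-Dindo grade 2 or higher up to 30 days after surgery.

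The Discussion reports LE complication figures from two of the references behind the 15%. One is the institution's own earlier series, with one patient (2.1%) whose complication prolonged the hospital stay. The other is a prospective study in T2 disease, with 21% of patients having events above grade 3 and 65% having grade 1 or 2 complications.

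**The concern.** A non-inferiority claim rests on one limit of one confidence interval. At one-sided 0.05 that is the upper limit of a two-sided 90% interval; at two-sided 0.05 it is the upper limit of a 95% interval. The sentence contains both "two-sided non-inferiority test" and "a significant level of 0.05, one-sided", and the unsided criterion under Data analysis does not choose between them. The same data could therefore meet the margin under one reading and miss it under the other.

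The stated 67 per arm should also follow from the inputs beside it. If it does not, the 80% power reported to readers and to the ethics committee is not the power of the design, and the size of the gap depends on which side is meant.

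**Working it through.** **Inputs** (all from Sample size calculation): rate 0.15 in each arm, so the true difference is 0; margin 0.15, taken here as an absolute difference in proportions; power 80%; 1:1 allocation; 67 per arm; 5% dropout; 140 enrolled.

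**1. Trying to reproduce 67.** The unpooled normal approximation for non-inferiority of two proportions is

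n per arm = (z_alpha + z_power)² × [p1(1 − p1) + p2(1 − p2)] / margin²

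where the variance sum is 2 × 0.15 × 0.85 = 0.255 and margin² = 0.0225.

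- One-sided 0.05: (1.645 + 0.842)² × 0.255 / 0.0225 = 70.07, so **71**.
- One-sided 0.025 (two-sided 0.05): (1.960 + 0.842)² × 0.255 / 0.0225 = 88.95, so **89**.

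Other choices do not give 67 either: one-sided 0.10 gives 52; at one-sided 0.05, the Farrington-Manning variance gives 75, a continuity correction 83 and the arcsine method 94.

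**2. Power at 67 per arm.** The standard error is √(0.255/67) = 0.0617, and 0.15/0.0617 = 2.431.

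- One-sided 0.05: Φ(2.431 − 1.645) = **78.4%**. Exact enumeration gives 78.6% for the unpooled (Wald) test and 76.8% for the Farrington-Manning test.
- One-sided 0.025: Φ(2.431 − 1.960) = **68.1%**.

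**3. Dropout.** 2 × 67 = 134. Dividing by 0.95 gives 141.05, so 142; multiplying by 1.05 gives 140.7. The stated 140 is therefore close to a 5% inflation of 134. Taking 5% off again, 140 × 0.95 = 133 evaluable, about 66.5 per arm. Power at 66 per arm is 77.9% or 67.5% on the two readings, so 133 evaluable gives about 78% or about 68%.

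For 80% power:

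| Reading | Evaluable | Enrolled with 5% dropout |
|---|---|---|
| One-sided 0.05 | 2 × 71 = 142 | 142/0.95 = 149.5, so 150 |
| Two-sided 0.05 | 2 × 89 = 178 | 178/0.95 = 187.4, so 188 |

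**4. Sensitivity to the LE rate.** With 15% after total mesorectal excision (TME), 67 per arm and one-sided 0.05, power = Φ{[0.15 − (p_LE − 0.15)] / √[(p_LE(1 − p_LE) + 0.1275)/67] − 1.645}.

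| LE rate | Power |
|---|---|
| 10% | 97% |
| 15% | 78% |
| 18% | 59% |
| 21% | 39% |

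**The case against.** **On the side of the test.** Non-inferiority is one-sided by nature, the alpha is given outright as one-sided, and 67 is near 71 and far from 89. The calculation was therefore probably meant at one-sided 0.05, and the 68% belongs to a level the article does not spell out. This is a fair reading and the more likely one. It does not remove the contradiction, because the sentence also says two-sided and no other section settles it.

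**On the size of the shortfall.** At one-sided 0.05 the gap is 1.6 percentage points. Exact power of the Wald test is saw-toothed: 68 per arm gives 80.03% and 69 gives 79.6%. The 70 per arm enrolled would give 79.97% by formula before any loss. All of this stands, and on that reading the shortfall is minor.

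**On dropout.** A reader might infer that the 5% was never added, or that 67 is 70 less 5%. The article does not support either. It goes from 134 to 140, within one or two patients of a correct inflation, and nothing in it says how 67 arose. What remains is only that 133 evaluable is below the recomputed 142.

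**On the LE rate.** A reader might also infer that the Discussion contradicts the equal 15% rates, since it reports 21% above grade 3 in one source and says that "the rate of overall complications including dehiscence of the rectal suture line resulted from anal pain are higher than TME". The text does not go that far. The same sentence says LE complications are generally less severe, and more events overall can coexist with equal rates at grade 2 or higher. The two LE figures, 2.1% and 21%, lie on either side of 15%. The 21% comes from T2 disease, whereas this trial enrols T3 or N+, and neither its time window nor its grading system is given. The 65% combines grades 1 and 2 and cannot be mapped to the endpoint. There is tension that calls for a sensitivity range, but no contradiction.

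**Conclusion.** The statement is wrong as written on two counts. The test is given two sides, which leaves the deciding interval open. And 67 per arm is not the number that the stated inputs produce: 71 are needed at one-sided 0.05 and 89 at two-sided 0.05. The 80% should read about 78% on the likelier reading, or about 68% on the other. The first is a small error in a central figure; the second would be a loss of about 12 percentage points.

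These results assume the margin is an absolute difference of 15 percentage points, 1:1 allocation, true rates of 15% in both arms and the unpooled normal approximation. The exact calculations at 67 per arm agree to within about 2 points. The LE rate is a secondary matter: the range of figures in the Discussion makes power sensitive to it, but does not show 15% to be wrong.

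**What to change.** 1. Delete the word two-sided. State a one-sided alpha of 0.05, with non-inferiority concluded if the upper limit of the two-sided 90% confidence interval for the LE minus TME difference in complication rates lies below 15 percentage points. Make the criterion under Data analysis agree for the primary endpoint.
2. Restate the power: 140 enrolled with 5% dropout leaves 133 evaluable and gives about 78% power at 15% in both arms. If two-sided 0.05 is what was intended, state the 95% interval and about 68% power instead.
3. If 80% power is to be kept as a claim, state 71 evaluable per arm and 150 enrolled (one-sided 0.05), or 89 per arm and 188 enrolled (two-sided 0.05).
4. Add the power at LE rates of 10%, 15%, 18% and 21%, with a short reason for choosing 15% for events of grade 2 or higher.

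Items 1, 2 and 4 change wording only and need no extra patients; the cost is a somewhat less favourable power figure. Item 3 would add 10 or 48 patients to the planned 140.

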## Background

In the treatment of rectal cancer, total mesorectal excision (TME) improves oncologic outcomes and adding preoperative chemo-radiotherapy (pre-CRT) to TME has been shown to effectively improve local control [1–4]. For this reason, pre-CRT followed by TME is recommended for patients with locally advanced mid-to-low rectal cancer [5–9]. However, significant complications are associated with TME, including anastomotic leak, sexual and urinary dysfunction, and frequent stool passage, on top of the peri-operative morbidity associated with all major surgery [10–12]. In addition, abdominoperineal resection (APR) involves a permanent stoma and low anterior resection (LAR) often involves at least a temporary stoma [8, 12, 13]. The decision of a surgical strategy must take oncologic outcomes, postoperative complications, and quality of life into account.

For patients with favorable responses to pre-CRT, organ-preserving strategies such as local excision (LE) and watchful waiting are becoming more accepted [14–19]. There has been some debate regarding the oncologic safety of LE following pre-CRT in advanced mid-to-low rectal cancer [14–18]. LE following pre-CRT for advanced rectal cancer could be a particularly good option for patients showing a complete pathologic response and achieving tumor regression not only in the primary tumor but also in the mesorectal metastatic lymph nodes [20–24]. Although the tumor regression grade (TRG) obtained using high-resolution rectal magnetic resonance imaging (mrTRG), as proposed by the MERCURY study group, correlated with the pathologic TRG [20, 21, 23, 24], mrTRG did not reflect the pathologic T status. A recent study from our institution showed that a status of mrTRG1 predicted a pathologic complete remission (pCR) with 60.6% accuracy and the projected completion TME rate of mrTRG1 was 25.6%. This results suggests that LE, compared with watchful wait, is more likely to result in pCR [25].

There have been several reports on the feasibility of performing LE following pre-CRT, most of which are focused on either clinical T2–3 rectal cancer or on cases of pCR [26–28]. However, the oncologic safety of LE in patients with a pathologic early T status after pre-CRT has not been established [29]. Therefore, data on long term outcomes with respect to the pathologic status and the type of surgery in patients with locally advanced rectal cancer is needed.

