### Study population

Patients who were diagnosed with pathologically confirmed rectal adenocarcinoma < 8 cm from the anal verge with clinically T3 or N+ before pre-CRT and an mrTRG grade 1 or 2 based on post-CRT images will be eligible for the study when they meet the following inclusion criteria:Male and female patients between the age of 20 and 80;Good performance status (ECOG performance status < 2);Capable of providing informed consent.

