#### Investigational treatment of the experimental arm

LE will be performed via conventional transanal excision or transanal minimal invasive surgery. During LE, remnant scar tissue will be excised with at least a 1 cm resection margin. Patients who have poorly differentiated or mucinous ypT2 tumors with lympho-vascular invasion, perineural invasion, tumor budding, and close resection margins (< 1 mm) will be recommend for TME within 3 months. If the patient undergoes TME, he or she will be evaluated as part of the TME group. If the patient does not choose to undergo TME, he or she will be excluded from the study and followed-up for additional subgroup analysis.

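### Reclassifying or excluding LE patients on pathology conflicts with the modified ITT set, and the 5% dropout allowance leaves no room for it

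*Protocol article*

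**What the plan says.** Four parts of the protocol article bear on this.

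- **Sample size calculation.** The design is a "two-sided non-inferiority test with for 80% power and a significant level of 0.05, one-sided". The assumed 30-day complication rates are "15% in the TME group and 15% in the LE group, with a non-inferiority margin of 15" per cent. From this, "a total of 67 patients should be allocated to each group", and "assuming a 5% dropout rate, we plan to enroll 140 patients".
- **Investigational treatment of the experimental arm.** LE patients with listed adverse pathology are advised to have TME within 3 months. Those who have it are evaluated with the TME group. Of a patient who declines, the text says "he or she will be excluded from the study and followed-up for additional subgroup analysis". No matching rule exists for the TME arm.
- **Data analysis.** The primary and secondary endpoints use the modified ITT set, defined as everyone who undergoes pre-CRT. The ITT set is everyone randomised.
- **Background.** An earlier study at the institution is cited: "the projected completion TME rate of mrTRG1 was 25.6" per cent. No rate is given for mrTRG 2, although a patient with "an mrTRG grade 1 or 2 based on post-CRT images will be eligible for the study", and the expected mix of the two grades is not stated.

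**The concern.** The LE section and the Data analysis section give different answers about who is analysed. Pre-CRT comes before randomisation, so the modified ITT set as defined drops no randomised patient because of pathology. The LE section does drop those who decline TME. For those who accept, it assigns an arm other than the randomised one, and the Data analysis section does not say in which arm a patient is counted.

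Two things are at stake. First, precision: if the LE section governs, patients leave the LE group for a reason that the 5% allowance does not cover. Second, validity: the trigger is a pathology result known only after randomisation and surgery, and it acts in one arm only. Patients taken out of LE are those with the worse pathology, and those moved are added to the comparator. The groups compared are then no longer the randomised groups, and a larger sample would not repair that.

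**Working it through.** **Inputs** (Sample size calculation): complication rate 15% in each arm, margin 15 percentage points, 80% power, 67 per group, 140 enrolled, 5% dropout. The sentence on the test names both two-sided and one-sided. I use one-sided 5%, the reading that comes closer to 67 (one-sided 2.5% would need 89 per group). The 25.6% comes from the Background.

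**Step 1: the plan's own figure.** With the unpooled normal approximation,

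n per group = (z0.95 + z0.80)² x [0.15 x 0.85 + 0.15 x 0.85] / 0.15² = (1.645 + 0.842)² x 0.255 / 0.0225 = 70.07, so 71.

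The stated 67 is not reproduced exactly, but it is near. Power is

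Φ( 0.15 / √[0.1275/n_LE + 0.1275/n_TME] − 1.645 ).

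With 67 per group this is 78.4%. Exact enumeration of the Wald test gives 78.6% at 67 and 80.0% at 68.

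**Step 2: what the 5% allowance leaves.** 70 x 0.95 = 66.5 per group, with power 78.2%. This is the baseline without the LE rule. The allowance is fully used, so any patient leaving LE takes the arm further below 67.

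**Step 3: the LE rule applied.** Let q be the share of LE patients who leave. Then n_LE = 66.5 x (1 − q). If all leavers have TME, n_TME = 66.5 x (1 + q). If all decline, n_TME stays at 66.5. At q = 25.6%:

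- n_LE = 66.5 x 0.744 = 49.5.
- All moved: n_TME = 66.5 x 1.256 = 83.5, and power is 75.7%.
- All excluded: n_TME = 66.5, and power is 72.3%.
- Half and half: 74.2%.

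The true q is not in the document, so a range is needed:

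| Share leaving LE | LE remaining | Power, all moved to TME | Power, all excluded |
|---|---|---|---|
| 0% | 66.5 | 78.2% | 78.2% |
| 10% | 59.9 | 77.8% | 76.2% |
| 20% | 53.2 | 76.7% | 73.9% |
| 25.6% | 49.5 | 75.7% | 72.3% |
| 40% | 39.9 | 71.7% | 67.5% |

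**Step 4: cost of the rule itself at 25.6%.** 78.2 − 75.7 = 2.5 points if all move; 78.2 − 72.3 = 5.9 points if all are excluded. The remaining gap to 80% comes from the base calculation and the rounding to 140. Keeping 67 in LE under the rule would need 67 / (0.744 x 0.95) = about 95 randomised to LE, against 70 planned.

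These figures hold every complication rate at 15%. They describe precision only and say nothing about the bias.

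**The case against.** The strongest reply is that the Data analysis section settles the matter: the primary endpoint uses a set that removes nobody for pathology, so with analysis as randomised the LE arm loses no one to the rule and power stays at about 78%. This stands in part. The shortfall is conditional on the LE section taking precedence. But the Data analysis section fixes who is included, not the arm in which a moved patient counts, and the LE section is the only text that names an arm. For patients who decline TME the two sections cannot both be followed.

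A reader might also infer that the plan itself projects a quarter of LE patients to be lost. The document does not support that. The 25.6% refers to mrTRG 1 only, and the criteria behind it are not shown. The trial's own trigger is described in two ways: a set of ypT2 features in the LE section, and a wider group that includes ypT3 and ypT4 under Safety. The rate is also one of completion TME, and patients who have TME are moved, not lost. The 72% figure therefore describes an extreme in which all of them decline, and no refusal rate is given.

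It is fair, too, that the sample size section is silent on reclassification and does not misstate it, and that a 5% dropout allowance is not in itself a claim about pathology. What survives is that, under the LE rule, any share leaving pushes that arm below 67.

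**Conclusion.** The point holds in conditional form. The LE section and the modified ITT definition conflict, and the enrolment figure leaves no room for the LE rule. If that rule governs and 25.6% of all LE patients leave (an extrapolation from mrTRG 1), about 49 to 50 LE patients remain and power is about 72% to 76%. At 10% leaving it is about 76% to 78%, and at 40% about 67% to 72%. The right comparison is the 78% that the plan's inputs deliver without the rule, not the stated 80%.

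One might conclude that the dropout figure alone makes the stated power and group size wrong. That goes too far: the loss due to the rule is moderate, and part of the gap to 80% is there before it applies. The more serious consequence is the bias from a one-arm, post-randomisation reclassification. Its direction cannot be determined from the document.

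**What to change.** Reconcile the LE treatment section, the Sample size calculation and the Data analysis section as follows.

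- State that every randomised patient is analysed in the allocated arm for the 30-day primary endpoint, whether or not completion TME follows. Withdraw the transfer to the TME group and the exclusion of those who decline, as far as this analysis is concerned.
- State that the 5% covers only loss before day 30.
- Restate power as about 78% for 66.5 to 67 evaluable patients per group at one-sided 5%.
- Say which operation starts the 30-day window for a patient who has both LE and TME.
- Keep analysis by treatment received, if wanted, as a secondary analysis labelled as non-randomised.

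Keeping the rule and only restating power at 72% to 76% would be honest about precision but would leave the bias in place.

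The cost is small: no extra patients, and one figure stated less favourably. Because the endpoint closes at 30 days while completion TME may come up to 3 months later, much of the LE outcome may already be observed when a patient would be moved or excluded. The clinical recommendation for completion TME is not affected, although its two descriptions (LE section and Safety) need to be brought into agreement.

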#### Randomization and data management

After checking the response of pre-CRT, the participants with mrTRG 1 or 2 tumor will be assigned using random-number table with sealed envelopes by an external research worker who control the data. According to mrTRG 1 or 2, the allocation sequence will be stratified. The external research worker will collect the data and a statistician who provided the sample size calculation and data analysis plan will be analyze the data. The data entry, coding, security and storage with backup will be processed by the external research worker and simultaneously the statistician will check the accuracy and the value of the data. After finishing the collection of data, the external research worker, the statistician will access the dataset and investigators will access after analyses of the dataset.

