**Methods:**

A prospective, double-arm, randomized, open-labeled, single center, clinical trial will be conducted in patients with mid-to-low rectal cancer whose tumors are mrTRG 1/2 after pre-CRT at the Asan Medical Center, Seoul, Korea, after approval from the Institution Review Board. Patient medical records will be de-identified using a serial number to protect personal information. Inclusion criteria will include rectal adenocarcinoma with an inferior border < 8 cm from the anal verge, mrTRG 1/2, age > 20, and provision of informed consent. Postoperative complications will be assessed by Clavien-Dindo Classification Grade. Oncologic and functional outcomes will be collected and risk factors related to these outcomes will be investigated.

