#### Postoperative follow-up schedule

Patients will be followed for 3-year after surgery. Follow-up will consist of a physical examination and blood tests, including carcinoembryonic antigen (CEA) levels every 6 months after surgery. Chest X-ray and abdomino-pelvic CT every 6 months after surgery, chest CT will be performed every 6–12 months, and colonoscopy performed at 6–12 months and 24–36 months after surgery (Table 1).

**Table 1 Tab1:** Follow-up schedule and study procedure for study cohort

Documentation	Restaging	LE vs. TME	Visit 1	Visit 2–6
Study procedures	Screening	Surgery	Checking complications	Routine checkup
Period after pre-CRT	4–8 weeks	4–8 weeks	8–16 weeks	Every 6 months after Op.
Getting permission	●			
Screening	●			
Assigning serial number	●			
Demographics	●			
Physical exam	●		●	●
Heart/ lung evaluation	●			
Chest CT	●			● (Selective)
APCT	●			●
MR, rectal cancer	●			● (Selective)
Endoscopy	●			● (Selective)
Laboratory test	●		●	●
Endorectal sonography	●			
Manometry/questionnaire	●			● (Selective)
Checking complications			●	●
Selection of surgery type		●		

*Pre-CRT* Preoperative chemoradiotherapy, *Op*., Operation, *LE* Local excision, *TME* Total mesorectal excision, *CT* Computed tomography, *APCT* Abdomino-pelvic CT, *MR* Magnetic resonance

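### The named between-group tests use neither the mrTRG stratum nor the pre-surgical functional scores; adding both costs only wording and helps mainly the functional endpoints

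*Protocol article*

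**What the plan says.** Four places in the protocol article bear on this.

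- **Randomization and data management:** "According to mrTRG 1 or 2, the allocation sequence will be stratified".
- **Data analysis, between-group tests:** the rule for binary endpoints such as complications is "Variables and outcomes will be analyzed using chi-square tests (for proportions) or Fischer’s exact test, as appropriate". A separate rule applies to scores and other measurements: "Continuous data will be analyzed using Student’s t-test or Mann-Whitney U tests, as appropriate". Time-to-event outcomes are handled as follows: "Cumulative risk rates will be calculated using the Kaplan-Meier method and compared using log-rank tests". None of these sentences mentions mrTRG, a stratified form of the test or a baseline value.
- **Data analysis, modelling:** "Multivariate analyses using binary logistic regression will be used to assess the risk of postoperative complications". No covariates are listed. The abstract's Methods paragraph describes the related aim in these terms: "Oncologic and functional outcomes will be collected and risk factors related to these outcomes will be investigated".
- **Postoperative follow-up schedule, Table 1:** the row "Manometry/questionnaire" is marked at restaging, which precedes surgery. It is marked again at visits 2 to 6, there as selective.

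Secondary study endpoints sets quality of life and the Wexner score at 6, 12 and 24 months. Secondary outcomes measures also lists the LARS score and manometry.

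**The concern.** Two sources of information are in the design but not in the named tests, and they act differently.

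**mrTRG.** Stratified allocation balances the arms on mrTRG. If mrTRG predicts the outcome, the treatment difference already varies less from sample to sample. A test that ignores the stratum still uses the larger, unstratified standard error, so it is somewhat conservative and loses a little power. The Background and Discussion link mrTRG 1 to pathologic complete remission, and complete remission to better prognosis. A link with DFS, OS and recurrence is therefore plausible. The article gives no evidence of a link with 30-day complications.

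**Baseline functional scores.** These are not a stratification factor, so a chance imbalance between arms passes straight into an unadjusted comparison. The test keeps its nominal level, but the estimate is noisier than it need be. Function is a central part of the Discussion's argument for LE, and the trial plans only 67 evaluable patients per arm.

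**Working it through.** **Plan's own figure first.** Inputs from Sample size calculation: 15% complications in both arms, margin 15 points, one-sided 0.05, 80% power.

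n per arm = 2 × 0.15 × 0.85 × (1.645 + 0.842)² / 0.15² = 70.07, so 71. The article states 67. At 67 per arm:

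- SE = √(2 × 0.1275 / 67) = 0.0617
- power = Φ(0.15/0.0617 − 1.645) = 78.4%

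The 67 versus 71 gap is a separate matter. Here 78.4% serves only as the unadjusted reference.

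**Primary endpoint, stratified by mrTRG.** The article gives neither complication rates by mrTRG nor stratum sizes. Both are assumed, with the overall rate held at 15%. For a share w in the lower-rate stratum:

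- unstratified variance v₀ = 0.15 × 0.85 = 0.1275
- within-stratum variance v = w·p₁(1 − p₁) + (1 − w)·p₂(1 − p₂)
- stratified power = Φ(0.15/√(2v/67) − 1.645)
- true one-sided level of the unadjusted test ≈ 1 − Φ(1.645·√(v₀/v)), using the equal-rate variances as an approximation

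| Shares | Stratum rates | v/v₀ | Variance removed | Power, stratified | Level, unadjusted |
|---|---|---|---|---|---|
| any | 15% / 15% | 1.000 | 0% | 78.4% | 0.050 |
| 50:50 | 10% / 20% | 0.980 | 2.0% | 79.1% | 0.048 |
| 50:50 | 5% / 25% | 0.922 | 7.8% | 81.3% | 0.043 |
| 30:70 | 10% / 17.1% | 0.992 | 0.8% | 78.7% | 0.049 |
| 30:70 | 5% / 19.3% | 0.966 | 3.4% | 79.6% | 0.047 |

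The 50:50 rows can be checked by hand: (0.05² / 0.1275) = 2.0% and (0.10² / 0.1275) = 7.8%.

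**Functional scores, adjusted for baseline.** The article gives no baseline to follow-up correlation r, so it is assumed. ANCOVA multiplies the variance by 1 − r². The equivalent unadjusted sample is 67/(1 − r²). The unadjusted detectable difference at 80% power is (1.960 + 0.842) × √(2/67) = 0.484 SD, and ANCOVA scales it by √(1 − r²). Power is for an assumed true difference of 0.4 SD, two-sided 0.05, with all 67 per arm measured.

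| r | Variance removed | Equivalent n per arm | Detectable difference | Power at 0.4 SD |
|---|---|---|---|---|
| unadjusted | none | 67 | 0.484 SD | 63.9% |
| 0.3 | 9% | 74 | 0.462 SD | 68.0% |
| 0.5 | 25% | 89 | 0.419 SD | 76.2% |
| 0.6 | 36% | 105 | 0.387 SD | 82.5% |

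A simulation agrees: about 63% power unadjusted, and 66% and 75% with ANCOVA at r = 0.3 and 0.5. In patients, 1/0.91 = 1.10 and 1/0.64 = 1.56, so adjustment is worth 10% to 56% more patients among those with both measurements.

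**If change scores were meant.** Their variance factor is 2(1 − r): 1.40, 1.00 and 0.80 at r = 0.3, 0.5 and 0.6. ANCOVA gives 0.91, 0.75 and 0.64, which is lower each time.

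**Survival endpoints.** The article gives no event rates, so no gain is computed.

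**The case against.** **The article names test families, not full specifications.** A log-rank test can be stratified, the t-test might be applied to changes from baseline, and the article refers to a data analysis plan that is not shown. This stands in part: the unseen plan may already stratify. But the article does fix the tests, and as written they do not reflect its own allocation scheme.

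**An adjusted analysis of the primary endpoint is planned.** A reader might infer that every planned analysis is unadjusted. The logistic regression rules that out. It does not close the gap, however. Its covariates are unnamed, it reads as risk-factor work, it yields an odds ratio rather than a difference to compare with 15 points, and it does not cover functional or survival outcomes.

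**The primary analysis is not invalid.** A reader might infer that ignoring the stratum undermines the non-inferiority conclusion, or makes the reported intervals too wide. The documents support neither. The unadjusted test errs slightly towards caution, so this omission does not favour a false claim of non-inferiority. Data analysis mentions no confidence interval that could be called too wide.

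**The functional gain is conditional.** This stands. The correlation is assumed, the endpoints are secondary with no stated power target, and follow-up measurement is selective. The Discussion also reports about 30% permanent stomas after TME in the institution's own series, which may further limit continence and manometry data. Baseline adjustment does not repair missing follow-up.

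**Conclusion.** The point holds as a free improvement. The named between-group tests use neither the randomisation stratum nor the scheduled pre-surgical functional scores, and no planned analysis clearly supplies an adjusted LE versus TME comparison.

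- **Primary endpoint:** a small effect, 0 to 3 power points. The upper end needs a fivefold difference in complication rates between equal strata. Here the case for stratifying is mainly consistency with the design.
- **Functional scores:** the more useful gain. It applies in proportion to patients with both baseline and follow-up values, so the figures at 67 per arm are an upper bound on what selective follow-up can deliver.
- **Survival endpoints:** the direction is plausible, the size unknown.

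**What to change.** Amend Data analysis before any outcome data are compared:

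1. **Primary endpoint:** report the LE minus TME risk difference with a confidence interval stratified by mrTRG (Mantel-Haenszel or stratified Miettinen-Nurminen), and judge it against the 15-point margin. Describe the logistic regression as a risk-factor analysis and list its covariates.
2. **DFS, OS and recurrence:** use log-rank tests stratified by mrTRG.
3. **QLQ-C30 and Wexner score at 6, 12 and 24 months, and LARS score and manometry where measured:** use ANCOVA or a mixed model with mrTRG and, where a baseline measurement exists, the baseline value. State which instruments are taken at restaging, since Table 1 does not name the questionnaires.

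Report how many patients in each arm have both baseline and follow-up values, so that readers can judge the effect of selective measurement.

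The cost is analysis wording. mrTRG is known for every randomised patient and the baseline assessment is already scheduled, so no extra patients or visits are needed. Check that the named software (SPSS version 22) produces the stratified risk difference; with two strata it can otherwise be computed directly.
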